## Abstract

Supplemental Digital Content is available in the text

## Introduction

1

Mild cognitive impairment (MCI) is a transitional state from normal aging to dementia. The Diagnostic and Statistical Manual of Mental Disorders (DSM-5) criteria for diagnosis of MCI is that cognitive decline is present in 1 or more cognitive domains (complex attention, executive function, learning and memory, language, perceptual-motor, and social cognition) but does not interfere with independence in daily activities.^[1]^ MCI is considered a prodromal stage of dementia—10% to 15% of patients with MCI develop Alzheimer's disease every year, given a 1% to 2% annual progression rate in the normal population.^[2]^ However, while diverse pharmacological and cognitive interventions are under investigation, the evidence regarding effective therapies for MCI is still limited;^[3,4]^ consequently, as per the established guidelines, pharmacological treatment is only recommended for symptomatic treatment.^[5]^

Pharmacopuncture is a treatment that involves the insertion of medication to be embedded into a specific acupoint. It is a combined form of acupuncture and herbal medicine and is applied for the treatment of diverse diseases including neuropsychiatric diseases. Two randomized control trials showed that pharmacopuncture combined with oral administration of other drugs had better effects on the cognition of patients with Alzheimer disease than oral administration itself or intramuscular injection combined with oral administration.^[6,7]^

*Hominis placenta* (*H placenta*) is human placenta and contains immune substances such as interferons, blood coagulation factors, hormones and their precursors, and cell proliferation factors. In traditional medicine, *H placenta* was used for treating memory loss, agitation, and disorientation, which are now known to be consistent with major symptoms of dementia. Animal experiments revealed that *H placenta* itself or medication containing *H placenta* increased both learning and memory ability and brain-derived neurotrophic factor expression in the brain.^[8–10]^ Recently, several randomized controlled trials and case studies were conducted on the treatment of dementia using oral administration of medication containing *H placenta*.^[11–17]^

Considering results from a series of preclinical studies and a case report, it was considered important to conduct a randomized controlled trial examining whether *H placenta* pharmacopuncture improves memory. Thus, the aim of this study is to investigate the effect of *H placenta* pharmacopuncture versus saline pharmacopuncture on patients with MCI with regard to aspects of memory and accompanying symptoms related to mood, sleep, and quality of life after 8-week administration.

## Methods

2

### Objectives

2.1

The aim of this study is to explore the efficacy and safety of *H placenta* pharmacopuncture in patients with MCI. To this end, the trial is designed to evaluate its efficacy on cognitive functions assessed using the MoCA-K, MMSE-DS, K-DRS, Clinical Dementia Rating (CDR), and Global Deterioration Scale (GDS) and to assess mood change, sleep disturbance and quality of life using the Korean version of Beck Depression Inventory-II (K-BDI-II), State-Trait Anxiety Inventory (STAI), State-Trait Anger Expression Inventory (STAXI), Insomnia Severity Index (ISI), Euro Quality of Life - 5 Dimensions (EQ-5D), Euro Quality of Life - visual analog scale (EQ-VAS), and Geriatric Quality of Life scale-Dementia (GQOL-D).

### Design

2.2

This study is a randomized, double-blind, placebo-controlled, 2-center clinical trial to objectively evaluate the efficacy and safety of *H placenta* pharmacopuncture for MCI (Fig. 1). *H placenta* pharmacopuncture or placebo will be administered to participants for 8 weeks and changes in symptoms observed before and after 8 weeks of administration. This trial will be performed in Kyung Hee University Korean Medicine Hospital and Semyung University Korean Medicine Hospital. This protocol is presented in accordance with the Standard Protocol Items: Recommendations for Interventional Trials 2013 statement (see Table, Supplemental file 1, Fig. 2). The organizational structure and responsibilities of the researchers are shown in Supplemental file 2.

**Figure 1 F1:**
[figure not shown]
Diagram of the study flow.

**Figure 2 F2:**
[figure not shown]
Standard protocol items: recommendations for interventional trials statement. Overview of study process and outcome assessment.

### Ethical considerations

2.3

The Institutional Review Boards of Kyung Hee University Korean Medicine Hospital and Semyung University Korean Medicine Hospital approved the study (KOMCIRB 2019-10-004 and SMCJH 1912-08, respectively). This trial complies with the Declaration of Helsinki. Korean neuropsychiatrists will explain participant title, purpose, period, method, expected effect, risk, protection of the participants, consent for voluntary participation, and withdrawal of consent using the informed consent form. The participant will voluntarily decide whether to participate or not and will either sign or not sign, respectively, an informed consent form. Protocol amendments will be approved by IRB and these modifications will be updated in protocol registration site or a journal. If the modification results in alteration in their benefit or harm, participants will be notified. The results of the trial will be disseminated via publication in peer-review journals.

### Participants

2.4

#### Assessment of eligibility

2.4.1

Participants who voluntarily agree to the trial will be given a subject identification code in order, and undergo a demographic survey, vital sign and laboratory tests, and neuropsychological examinations to determine whether they meet the inclusion/exclusion criteria.

#### Inclusion criteria

2.4.2

(1)Male or female adult aged 50 to 80.(2)A person diagnosed with mild neurocognitive impairment based on DSM-5.(3)A person who can undergo neuropsychological tests and complete questionnaires.(4)A person who agrees to participate in the trial after receiving explanations regarding the purpose and procedures involved in the clinical trial and has signed the informed consent form by oneself or one's legal representative.(5)A person with a score of 0.5 on the CDR.

#### Exclusion criteria

2.4.3

(1)A person with a cranial lesion or brain injury that can cause cognitive decline.(2)A person with a history of cerebral hemorrhage or cerebral infarction.(3)A person with brain diseases such as Parkinson disease, epilepsy, and brain cancer.(4)A person with a present illness or past history of a major psychiatric disorder such as schizophrenia, delusional disorder, depressive disorder, bipolar disorder, or alcohol or substance abuse disorder as diagnosed using DSM-5.(5)A person who has participated in other clinical trials within the last 1 month.(6)A person who had acupuncture treatment for cognitive impairment within the last 4 weeks.(7)A person who is currently taking medication related to dementia (If the person is diagnosed with MCI and is taking dementia-related drugs, he/she may participate in the clinical trial after the wash-out period of 15 days).(8)A person with a severely destabilizing general medical condition (a doctor in charge will judge the enrollment based on the results of laboratory tests, vital signs, etc).(9)A person with a clinically serious liver disease or with serum aspartate transaminase and alanine transaminase levels exceeding twice the upper limit of reference value.(10)A person with chronic renal failure or with serum blood urea nitrogen and creatinine levels exceeding 1.5 times the upper limit of reference value.(11)Pregnant woman, lactating woman, or woman of childbearing potential who do not use appropriate methods of contraception.(12)A person who researchers judge to be inappropriate for participation in this clinical trial.(13)A person who is hypersensitive to *H placenta* and other drugs.(14)A person with moderate complications other than those involving the heart, liver, and kidney.(15)A person with psychogenic diseases.

#### Discontinuation criteria

2.4.4

Participants can be excluded from the study when any of the following conditions are met:

(1)In case the participant withdraws their consent to participate in the trial.(2)In case the participant violates the inclusion criteria or meets the exclusion criteria.(3)In case the participant has serious adverse events (AEs), or it is difficult to continue the clinical trial due to AEs.(4)In case it is judged impossible to continue treatment or observe the participant due to an unexpected disease or accident.(5)In case the participant requests discontinuation or the investigator determines discontinuation due to a worsening cognitive deficit during the clinical trial.(6)In case cognitive function deteriorates during the clinical trial and CDR becomes 1 or higher.(7)In case it is determined that there is an unavoidable reason for the participant to discontinue the trial.(8)In case overall compliance is less than 70%.

To promote compliance of participants, we plan to send a text message as a reminder a day before the appointment.

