### Interventions

2.7

Pharmacopuncture treatment will be performed by Korean neuropsychiatrists following the details of the Standards for Reporting Interventions in Clinical Trials for Acupuncture 2010 checklist (Table 1). Each participant will be scheduled to visit the institution twice a week for 8 weeks after screening and receive a total of 16 treatments of *H placenta* pharmacopuncture or placebo pharmacopuncture. 1 mL of *H placenta* or placebo will be injected twice a week into acupoints (GV20, both ST36, CV12). *H placenta* (Unimed Pharmaceutical, Seoul) is a pale-yellow transparent liquid contained in a brown ampoule. The content is 1 mL of *H placenta* extract per 1 mL. It should be stored in the shade in sealed containers at room temperature (1–30°C). Saline will be used as placebo; it is a colorless, clear liquid with a salty flavor. The content is 9 mg sodium chloride in 1 mL. Other drugs and therapies to ameliorate cognitive function are prohibited in principle during the clinical trial period, and in the event of concurrent treatment, the clinical trial director will determine whether the participant will be excluded from the study and the statistical analyses.

**Table 1 T1:** Details of acupuncture intervention (STRICTA).

Item	Detail	Description
Acupuncture rationale	(1a) Style of acupuncture	Pharmacopuncture
	(1b) Reasoning for treatment	The treatment was selected based on previous studies such as animal experiments and a case report.
	(1c) Extent to which treatment varies	None
Details of needling	(2a) Number of needle insertions per subject per session	4
	(2b) Names of points used (unilateral/bilateral)	GV20, CV12, ST36 (bilateral)
	(2c) Depth of insertion	5–10 mm
	(2d) Response sought	None
	(2e) Needle stimulation	None
	(2f) Needle retention time	None
	(2g) Needle type	0.30 mm × 8 mm, single use syringes (Becton, Dickinson and Company, USA)
Treatment regimen	(3a) Number of treatment sessions	16 sessions
	(3b) Frequency and duration of treatment sessions	2 sessions/wk for 8 wk
Other components of treatment	(4a) Details of other interventions administered to the acupuncture group	None
	(4b) Setting and context of treatment	Hospital outpatient department
Practitioner background	(5) Description of participating acupuncturists	Korean neuropsychiatrist or Korean medical doctor with an experience of more than 1-yr under the guidance of a Korean neuropsychiatrist

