#### Primary outcome

2.8.1

The primary outcome is the difference in mean change of MoCA-K scores between intervention group and control group. The MoCA-K is a tool that was originally developed by Nasreddin et al.^[21]^ to screen for MCI, which was translated into Korean and validated. It consists of 7 areas to evaluate memory, visuospatial/ executive function, naming, attention, language, abstraction, and orientation. The maximum score is 30 points, and 1 point is added when the participant has been educated for less than 6 years to correct differences in cognition due to academic background. It suggests a cutoff point of 22 or less for screening MCI,^[22]^ which means a decrease in cognitive function. Reliability of the original tool was Cronbach's α =.83^[21]^ and that of the translated tool was Cronbach's α =.81–.84.^[22]^

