#### Secondary outcomes

2.8.2

Secondary outcomes are

(1)differences in mean change of MMSE-DS, K-DRS, CDR, GDS, K-BDI-II, STAI, STAXI, ISI, EQ-5D, EQ-VAS, and GQOL-D scores between intervention group and control group, and(2)direction of intra-group change of mean of K-DRS, MMSE-DS, MoCA-K, CDR, GDS, K-BDI-II, STAI, STAXI, ISI, EQ-5D, EQ-VAS, and GQOL-D scores in pre- and post-treatment evaluation. K-DRS, MMSE-DS, MoCA-K, GDS, K-BDI-II, STAI, STAXI, ISI, EQ-5D, EQ-VAS, and GQOL-D scores will be assessed at baseline and 8 weeks, and CDR score will be assessed at baseline, 4 weeks, and 8 weeks.

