### Statistical analysis

2.10

Among the demographic data, continuous data will be presented as mean and standard deviation, and categorical data will be presented as frequency and percentage. Group comparison of continuous demographic data will use the *t*-test if normality is satisfied in and the Wilcoxon rank sum test if normality is not satisfied. Categorical data will be compared using the Chi-square test or Fisher exact test.

The independent sample *t*-test will be applied for comparison of the difference in the mean change in parameter before and after the clinical trial between intervention group and the control group, and the Wilcoxon rank sum test can be applied when nonparametric analysis is required. In order to compare the difference in the change in trend by each group visit, data will be analyzed using repeated measures analysis of variance. All the statistical tests will adopt 2-tailed testing considering an alpha value of 0.05 with 80% power. Intent to treat will be mainly performed, but per-protocol will also be performed as a supplement.

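### Intention-to-treat is the named main analysis, but section 2.7 lets randomised participants be dropped from the analyses case by case, and section 2.4.4 can remove decliners before the only post-baseline MoCA-K

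*Protocol article*

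**What the plan says.** Four parts of the Protocol article bear on who is analysed.

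- **2.10 Statistical analysis** sets the hierarchy: "Intent to treat will be mainly performed, but per-protocol will also be performed as a supplement".
- **2.7 Interventions** prohibits other cognitive treatment in principle. If it occurs, "the clinical trial director will determine whether the participant will be excluded from the study and the statistical analyses". No criterion for the decision is given, and it is not confined to the per-protocol set.
- **2.4.4 Discontinuation criteria** opens with "Participants can be excluded from the study when any of the following conditions are met". Among the eight conditions are a participant request or the case where "the investigator determines discontinuation due to a worsening cognitive deficit during the clinical trial" (condition 5), "In case cognitive function deteriorates during the clinical trial and CDR becomes 1 or higher" (condition 6), "In case overall compliance is less than 70" per cent (condition 8), and an eligibility violation (condition 2).
- **2.8.1 and 2.8.2** define the endpoint and its timing: "The primary outcome is the difference in mean change of MoCA-K scores between intervention group and control group". MoCA-K is in the list of scales that ends "EQ-5D, EQ-VAS, and GQOL-D scores will be assessed at baseline and 8 weeks". CDR has an additional assessment at week 4.

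**The concern.** An intention-to-treat analysis keeps everyone as randomised. A rule that lets someone decide after randomisation, without stated criteria, that a participant leaves the analyses is incompatible with it. Participants who seek other cognitive treatment may well be those who feel they are declining, so this discretion need not be unrelated to outcome.

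Section 2.4.4 works less directly. Conditions 5 and 6 select on cognition, which is the domain of the primary endpoint. If exclusion from the study also ends assessment, a participant excluded before week 8 has no change score for the planned t-test.

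Conditions 2 and 8 are different. They are post-randomisation selection, which weakens the randomised comparison, but they are not direct selection on the outcome.

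**Working it through.** **1. The texts side by side.** Section 2.10 says that the main analysis is by intention-to-treat. Section 2.7 says that a randomised participant may be excluded from the statistical analyses by a case-by-case decision. Without a restriction to the per-protocol set, both cannot hold. This needs no arithmetic.

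**2. The timing.** CDR is assessed at weeks 0, 4 and 8, and MoCA-K at weeks 0 and 8. A CDR of 1 or higher at week 4 can trigger exclusion four weeks before the only post-baseline MoCA-K. At week 8 both scales are due together, so condition 6 threatens the primary value mainly at week 4. Condition 5 has no fixed time.

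**3. The plan's own numbers.** Section 2.9 gives 10 evaluable per group and 30% dropout. 10 / (1 − 0.30) = 14.3, rounded up to 15 per group, which reproduces the stated 15 per group and 30 in total. (Section 2.6 reads as 30 in each group. That is a separate matter; 15 per group is used here.)

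**4. How often condition 6 might act.** The Introduction gives 10% to 15% progression to Alzheimer's disease per year. Treating that, as an approximation, as the rate of reaching CDR 1, and pro rata over 4 of 52 weeks among 30 participants: 30 × 0.10 × 4/52 = 0.23 and 30 × 0.15 × 4/52 = 0.35. So about 0.2 to 0.35 participants, both arms together, are expected by week 4. Condition 5 could add more, at a rate that the document does not allow one to estimate.

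**5. Common threshold, applied blind.** Assume normal change scores with SD 1, mean 0 on placebo and d on active, and remove everyone below a threshold c. The observed difference is d + φ(c − d)/[1 − Φ(c − d)] − φ(c)/[1 − Φ(c)].

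- With 20% of placebo patients removed, c = −0.842 and the placebo mean rises by 0.280/0.80 = 0.350.
- With d = 0.50, 9.0% of active patients are removed and their mean rises by 0.162/0.910 = 0.178. Observed difference: 0.50 + 0.178 − 0.350 = 0.328 SD.
- With 10% or 30% of placebo patients removed, 0.50 becomes 0.39 or 0.28 SD.
- With d = 0, both arms shift equally and the expected bias is 0.
- If the removal marker correlates only 0.5 with MoCA-K change, 0.50 becomes 0.45, 0.41 or 0.39 SD for 10%, 20% or 30% removed.

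**6. Worst case: losses in one arm only.** For 15 normal values, the expected lowest three are −1.736, −1.248 and −0.948 SD. The rise in the mean after removing the lowest k is the sum of their absolute values divided by (15 − k).

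| Lowest removed | Calculation | Shift (SD) |
|---|---|---|
| 1 | 1.736/14 | 0.12 |
| 2 | 2.984/13 | 0.23 |
| 3 | 3.932/12 | 0.33 |

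For scale, the standard error of the group difference with 15 per group is √(2/15) = 0.37 SD.

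**The case against.** Section 2.4.4 stands under a discontinuation heading, is permissive, and does not mention the analysis. A reader might infer from it that the main analysis will in fact lose decliners and become a per-protocol analysis in all but name. The document does not support that. An assessment at discontinuation or a method for missing week-8 values may be in the full protocol, in the schedule figure (not shown) or in a statistical analysis plan, and their absence from an article is no finding. This objection stands: for 2.4.4 the most that can be said is that a primary value may be missing. It does not reach 2.7, whose text names the analyses. Nor can an analysis plan recover measurements that were never taken.

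A reader might also infer that the bias favours the product, or that the whole 30% dropout allowance could be decliners. Neither is supported. Section 2.6 blinds practitioner, participant and assessor, so one-arm loss is a worst case; under blinding and no effect, losses should balance on average, and under benefit the observed difference shrinks. Section 2.9 attributes the 30% to the length of administration and follow-up, not to decline. On the Introduction's progression rates, week-4 exclusions for CDR should be rare.

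Finally, low compliance is not selection on outcome. Overall compliance may also be known only near the end, when the week-8 MoCA-K is due anyway. That too stands.

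**Conclusion.** The point holds in two parts of unequal strength. First, 2.7 and 2.10 contradict each other in their wording: discretionary removal from the analyses cannot coexist with an intention-to-treat main analysis. Second, 2.4.4 together with the assessment times allows missingness related to the outcome domain under conditions 5 and 6. Whether it would occur depends on whether exclusion ends follow-up, which the article leaves unclear.

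The size is uncertain and the direction is not fixed. Under normal change scores it runs from no expected bias (blinded, no effect), through attenuation of 0.50 to about 0.33 SD (common threshold, worst 20% of placebo patients removed), to a one-arm shift of about 0.12 to 0.33 SD for one to three losses. The last is a worst case, not a forecast. The point still needs correction before the trial starts, because it concerns the validity of the primary comparison in a trial of 15 per group and uncollected week-8 values cannot be recovered.

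**What to change.** 1. In 2.7, strike the words that extend exclusion to the statistical analyses. Let concurrent treatment, like compliance below 70%, affect only the per-protocol set, with membership decided before the A/B allocation table is released to the analyst (2.6).

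2. Reconcile 2.4.4 with 2.10 by adding a sentence: discontinuation under 2.4.4, whenever it is applied, does not end outcome follow-up. Unless consent to data collection is withdrawn, the scheduled week-8 MoCA-K is still obtained and the participant stays in the intention-to-treat analysis as randomised.

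3. Leave the clinical stopping criteria and their permissive wording as they are. Nothing here requires a view on them.

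The cost is two changes of wording and the already scheduled week-8 visit for the few participants who discontinue. The small downside is that some week-8 values will be off treatment and will dilute the effect slightly.

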### Recruitment

2.5

Participants will be recruited by posting documents at appropriate places such as bulletin boards in hospitals, community centers, and subways. During the recruitment process, participant anonymity will be maintained to protect personal privacy and ensure confidentiality. In addition, assigned personnel will respond to recruitment inquiries and keep the recruitment data in a space with limited access.

### Randomization, allocation concealment, and blinding

2.6

30 eligible participants each will be randomly assigned to the pharmacopuncture group and the placebo group in a 1:1 ratio. Block randomization will be performed on participants who meet the inclusion/exclusion criteria. The randomization number will be generated by an independent statistics expert. The generated number will be placed in a lightproof, sealed envelope and kept in a locked chamber that is accessible only to people authorized to be unblinded. After completion, database lockout will be performed, and then the random number table with intervention group or control group labelled either A or B will be provided to the investigator responsible for statistical analysis. After the statistical analysis is completed, the group information marked either A or B will be disclosed.

This clinical trial is designed to be double-blinded by separating the pharmacopuncture practitioner and assessor from the process of transferring *H placenta* from ampule to syringe and controlling the bias as much as possible. To avoid participant bias as much as possible, the syringe used will have a translucent tape on the surface to avoid the participant from noticing the color of the liquid. Participants will be informed that they have been allocated to 1 of 2 groups and receive the treatment in a clinic setting similar to where 1 generally receives treatment in Korean medicine hospitals or clinics. The practitioner will inject the same amount of *H placenta* or saline with the needle at the same acupoints so that both practitioner and participant do not infer allocation. The validity of the blinding will be assessed by an investigator who is not involved in either allocation or performance of the pharmacopuncture treatment. If an emergency occurs during the clinical trial, such as a serious AE (SAE), and it is absolutely necessary to protect the rights and safety of the participant, unblinding can be performed at the request of an investigator. The investigator should then report the details of the need for unblinding to the IRB.

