### Sample size calculation

2.9

Since there were no previous clinical trials on *H placenta* for this indication, the results of previous studies on herbal medicines using MoCA scores^[36]^ were cited. According to the previous study comparing MoCA scores after herbal medicine or placebo treatment of patients with MCI, calculation using a standard formula^[37]^ yielded a sample size of 10 for each group, with 80% statistical power at 5% level significance (α=0.05, 1-β=0.8). Assuming a dropout rate of 30% considering the 8-week-long administration and follow-up period, the final sample size will be 15 for each group, 30 in total.

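### Two-centre trial whose stated primary comparison ignores centre, and whose randomisation section does not say whether the blocks are stratified by centre

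*Protocol article*

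**What the plan says.** All references are to the protocol article.

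- Section 2.2 describes a "double-blind, placebo-controlled, 2-center clinical trial" and names the two hospitals.
- Section 2.6 gives the allocation method: "Block randomization will be performed on participants who meet the inclusion/exclusion criteria". It adds a 1:1 ratio, numbers generated by an independent statistician, and sealed envelopes. It states no block size and no stratification factor. It does not say whether there is one list or one per hospital.
- Section 2.8.1 makes the between-group difference in mean MoCA-K change the primary outcome. Section 2.8.2 places MoCA-K at baseline and week 8 only.
- Section 2.10 names the test for that contrast: "The independent sample *t*-test will be applied for comparison of the difference in the mean change in parameter". A Wilcoxon rank sum test replaces it when a nonparametric analysis is required. No centre term is mentioned.
- Section 2.9 states that the calculation "yielded a sample size of 10 for each group, with 80% statistical power at 5% level significance", raised to 15 per group and 30 in total for 30% dropout.
- On operators, the text of section 2.7 says "Pharmacopuncture treatment will be performed by Korean neuropsychiatrists", whereas Table 1 item 5 admits a "Korean neuropsychiatrist or Korean medical doctor with an experience of more than 1-yr under the guidance of a Korean neuropsychiatrist".

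**The concern.** The injection is given by hand at four points, and several outcomes are scored by an interviewer. Hospitals could therefore differ in how much MoCA-K changes over 8 weeks, through patient mix or through the way sessions and tests are run. In a trial of 30, a few patients decide whether the two arms have a similar site mix.

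The plan names a test that cannot take centre into account, and this matters under either reading of section 2.6. With one shared list, a chance imbalance by site passes uncorrected into the estimate. With one list per hospital, the design removes the imbalance, but the t-test still counts between-centre variation as noise and so gives back part of the benefit. At stake are the precision and credibility of a very small trial's primary result.

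**Working it through.** **Inputs from the article.** Two centres, 1:1 allocation, two-sided alpha 0.05, 10 evaluable per group, 30% dropout, 15 per group.

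**Assumptions (not in the article).** Enrolment equal between hospitals, block size 4, centre effect on MoCA-K change of 0 to 1 within-centre SD, all 30 patients analysed.

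**1. The plan's own figure.** 10/(1 − 0.30) = 14.3, rounded up to 15 per group. This reproduces. The 10 per group cannot be rebuilt, because no effect size or SD is given. Back-solving gives an implied standardised difference of (1.960 + 0.842) × √(2/10) = 1.25 by the normal approximation, or about 1.32 by the t-test. I use 1.25 as the true effect below.

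**2. Imbalance if one list is shared.** The SD of the between-arm difference in centre share is about √(0.5 × 0.5 × (1/15 + 1/15)) = 0.18. Simulation (40,000 trials per setting, blocks of 4) gives these chances of a difference of 20 points or more:

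- 33% when each patient is equally likely to come from either hospital;
- 40% when each hospital enrols exactly 15;
- 31% when one hospital is expected to supply a third of patients.

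With blocks of 6 the same three settings give 37%, 47% and 33%. Simple hypergeometric checks agree in scale: with 10 of 30 patients at one hospital, a 7:3 or worse split there has probability 2 × (0.0975 + 0.0225 + 0.0025 + 0.0001) = 0.245. With 15 at each, 10:5 or worse has probability 2 × (0.0581 + 0.0120 + 0.0013 + 0.0001) = 0.143.

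**3. Shift in the estimate.** The 95th percentile of the absolute imbalance is 0.33. Multiplied by a centre effect of 0.5 to 1 SD, this is a chance shift of 0.17 to 0.33 SD, or 13% to 27% of the implied 1.25 SD effect (0.17/1.25 and 0.33/1.25). The average imbalance is zero.

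**4. Error rate and power** (N = 30, exactly 15 per hospital, blocks of 4; model = linear model with treatment and centre):

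| Allocation | Centre effect | Type I, t-test | Type I, model | Power, t-test | Power, model |
|---|---|---|---|---|---|
| One list | 0 | 5.2% | 5.1% | 91% | 90% |
| One list | 0.5 SD | 5.0% | 5.0% | 90% | 90% |
| One list | 1 SD | 4.8% | 4.9% | 84% | 90% |
| Stratified | 0 | 4.9% | 4.9% | 91% | 91% |
| Stratified | 0.5 SD | 4.3% | 5.0% | 90% | 91% |
| Stratified | 1 SD | 3.0% | 5.0% | 86% | 91% |

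The conservative 3.0% can be checked by hand. With two equal centres 1 SD apart, the t-test's pooled variance is about 1 + 1²/4 = 1.25, so its standard error is too large by √1.25 = 1.118. The critical value of 2.048 (28 df) then acts as 2.048 × 1.118 = 2.29, and P(|t| > 2.29) is about 0.03.

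**The case against.** The strongest reply is that this is a condensed article, based on protocol version 1.7, which is not shown. Strata and block sizes are details that articles leave out. A reader might infer from section 2.6 that centre is not a stratum. The text does not say so, and an independent statistician can produce two lists as easily as one. That part of the reply stands: the imbalance figures are conditional on a shared list.

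Other stronger readings also fail.

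- *Operators and raters differ by hospital.* This is plausible, but operators are described by qualification only and assessors are not assigned to sites. The mismatch between section 2.7 and Table 1 item 5 is not linked to hospital and is no evidence about stratification.
- *The primary contrast is biased.* Under 1:1 randomisation the imbalance averages zero, and on one shared list the plain t-test keeps its error rate.
- *Treatment cannot be separated from site.* Not at the splits in question. For 10:5 and 5:10 the arm–centre correlation is 0.33 and the variance inflation is 1/(1 − 0.33²), about 1.13. For 7:3 and 8:12 it is 0.28 and about 1.09.

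It is also fair that a change score removes stable site differences in level, so only site differences in change matter, and no figure in the article shows that they are large. At 0.5 SD the power gain is 1 point or less.

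The reply does not reach the analysis. The test in section 2.10 is stated, and it takes no account of centre however the lists were made.

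**Conclusion.** The point holds as a modest, inexpensive improvement to a stated method: the primary comparison should include centre, and section 2.6 should say how the lists are organised. The harm is chance imbalance and lost precision. With one list, imbalance of 20 points or more occurs in about a third of trials (31% to 47% across the settings tried), and up to about 6 points of power are lost at a 1 SD centre effect. With stratified lists, the t-test's error rate falls to between 4.3% and 3.0% for centre effects of 0.5 to 1 SD, and about 5 points of power are lost at 1 SD.

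These sizes rest on assumed centre effects, enrolment shares and block sizes, and on N = 30. Section 2.6 also says "30 eligible participants each will be randomly assigned to the pharmacopuncture group and the placebo group in a 1:1 ratio", which read literally means 60 and conflicts with the 30 in section 2.9 and Table 2; the two must be reconciled. At N = 60 with blocks of 4, the chance of a 20-point imbalance on one list falls to about 16% (equal expected enrolment) or 20% (exactly 30 per hospital).

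**What to change.** - **Section 2.10.** For the primary outcome, replace the two-sample t-test with a linear model of MoCA-K change containing treatment and centre. If a nonparametric analysis is needed, use the centre-stratified rank test (van Elteren) instead of the plain Wilcoxon test.
- **Section 2.6.** State whether the blocks are stratified by centre. If they are not, generate a separate permuted-block list for each hospital. If allocation has already begun on one list, leave it; the centre term alone recovers most of the loss (84% to 90% in the 1 SD case).
- **Section 2.7 and Table 1 item 5.** As a separate matter, reconcile the two statements of operator qualification.

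The cost is one degree of freedom and two lists instead of one. If the centres do not differ, the model costs about 1 point of power on a shared list and almost nothing on stratified lists. No change in sample size is needed on this account.
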